The GenLinMixed models for the later follow-up tests are comparable, except they add a random intercept factor in addition to the baseline adjustment to account for any leftover correlations in the repeated data, which adjusts the error bands appropriately. Because all patients have received treatment at follow-up, direct testing of general treatment–control effects at follow-up is irrelevant (the *Group* factor). The estimable fixed factors thus become *Time* (1-post, 2-follow-up at 4 months and 3-follow-up at 12 months) and the *Time*Group* interaction that allows mean group differences at different time points. We will analyse if relapse occurs during the follow-up period by conducting repeated time series contrast analyses. In case of significant contrasts indicative of relapse, we will examine for possible differences between the SleepWell (early treatment) and the TAU (late treatment) study arms. Effect size statistics will be given as a standardised mean difference by dividing the beta-weight for a group comparison or a time difference with the within-subject standard deviation for the test, i.e. the residual SD.

The analyses will be conducted conservatively as intention-to-treat. Alpha values < 0.05 and 0.01 are assumed for the hypotheses about primary sleep treatment outcomes, i.e. SOL, WASO, SE and EMA, and secondary outcomes, i.e. affective health, fatigue and quality of life, respectively. The alpha value is set to 0.01 for analyses of moderators and mediators. The GenLinMixed handles missing data adequately without the need for multiple imputations, as it estimates the parameters based on all data available [82], thus reducing biases related to dropout given a missing-at-random (MAR) dropout pattern.

Since moderator variables in CBT-i are imperfectly understood [83], exploratory moderator analysis will extend the above regression models by adding the moderator variable with its two-way interactions with Time and Group to get a full three-way interaction that may discern exactly the subgroups defined by the moderator that benefit the most from treatment.

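### The follow-up model leaves out Group but keeps Time*Group, so that term tests any arm difference at any time and not whether relapse differs between the early- and late-treated arms

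*Protocol article*

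**What the plan says.** All statements are in the protocol article, section Statistical methods for primary and secondary outcomes {20a}.

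- On Group, the section reasons that since everyone has been treated by follow-up, "direct testing of general treatment–control effects at follow-up is irrelevant".
- From this it concludes: "The estimable fixed factors thus become *Time* (1-post, 2-follow-up at 4 months and 3-follow-up at 12 months) and the *Time*Group* interaction". The text describes that term as an "interaction that allows mean group differences at different time points". A baseline covariate and a random intercept complete the model.
- On relapse: "We will analyse if relapse occurs during the follow-up period by conducting repeated time series contrast analyses".
- If those contrasts are significant, "we will examine for possible differences between the SleepWell (early treatment) and the TAU (late treatment) study arms". The test for this last step is not named. Time*Group is the only listed fixed term that involves Group.

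**The concern.** Two things are run together. After crossover, Group no longer carries a treatment-versus-control meaning, and the plan is right not to test it as such. But Group still separates early from late treatment and can be estimated. Having no wish to test a main effect is not a reason to remove it while keeping its interaction.

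Removal changes what the interaction term means. The early-versus-late question is whether the arms change differently after post-test. Its null is equal change, which has 2 df with three time points. Without Group, the term's null is no arm difference at any of the three times, which has 3 df. A level difference that stays constant violates the second null and satisfies the first.

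Such a difference is possible. Under Participant timeline {13} the arms are assessed after treatment at weeks 16 and 32. The late arm has first waited about four months under usual care, and 20% dropout is allowed for. Baseline adjustment does not remove differences that arise after randomisation. At stake is a report that the timing of treatment affects how long benefit lasts, when the two trajectories are in fact parallel.

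**Working it through.** **1. What the term contains.** Let d1, d2, d3 be the arm differences at post-test, 4 months and 12 months.

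| Fixed part | Rank | Time*Group columns | Null of the term |
|---|---|---|---|
| Time + Time:Group | 6 | 3 (post, 4 m, 12 m) | d1 = d2 = d3 = 0 |
| Time + Group + Time:Group | 6 | 2 (4 m, 12 m, relative to post) | d1 = d2 = d3 |

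Both are the same six-cell model. Only the meaning of the term differs, and the plan's description matches the first row.

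**2. Inputs for an illustration.**
- From Sample size {14}: 68 × 1.25 = 85 patients, which is also what remains of 106 after 20% dropout (106 × 0.8 = 84.8). I split them 43 and 42. ICC 0.05.
- From {20a}: alpha 0.05 for primary sleep outcomes and 0.01 for secondary outcomes.
- Assumed, not in the document: baseline-adjusted SD 1; correlation ρ between post-treatment measurements 0.4 to 0.6; equal relapse in both arms; a constant offset d; 7 therapy groups per arm with a group effect stable over time; large-sample chi-square tests.

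**3. The 3-df test without clustering.** Noncentrality λ = d² × [1/(1/43 + 1/42)] × 3/(1 + 2ρ), where 1/(1/43 + 1/42) = 21.25.
- d = 0.4, ρ = 0.4: 0.16 × 21.25 × 3/1.8 = 5.67, rejection 49%.
- d = 0.4, ρ = 0.6: 0.16 × 21.25 × 3/2.2 = 4.64, rejection 41%.

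**4. The 3-df test with clustering**, total variance unchanged. λ = 3d² / [(1/43 + 1/42)(1 + 2ρ − 0.15) + (2/7)(0.15)], where 0.15 = 3 × 0.05.
- d = 0.4, ρ = 0.4: 0.48 / (0.0777 + 0.0429) = 3.98, rejection 36%.
- d = 0.4, ρ = 0.6: 0.48 / (0.0965 + 0.0429) = 3.44, rejection 31%.

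**5. Other offsets, alpha 0.05, same formulas.**

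| Constant offset (SD) | 3 df, no clustering | 3 df, ICC 0.05 | 2 df, Group kept |
|---|---|---|---|
| 0 | 5% | 5% | 5% |
| 0.2 | 13-15% | 11-12% | 5% |
| 0.3 | 24-29% | 19-21% | 5% |
| 0.4 | 41-49% | 31-36% | 5% |
| 0.5 | 61-70% | 47-54% | 5% |

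At alpha 0.01 and 0.4 SD the 3-df rates are 20-26% without clustering and 13-16% with it.

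The last column is flat because the 2-df test uses d2 − d1 and d3 − d2. Both are zero for a constant offset, so λ = 0.

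**6. Sensitivity to the variance assumption.** Measure the offset instead in unadjusted SDs, with the plan's pre-post correlation of 0.5 applied to all pairs of measurements. The adjusted variance is then 0.75, of which 0.25 is between patients. With 42 per arm and no clustering, d = 0.4 gives λ = 21 × 0.16 × 3/(0.75 + 2 × 0.25) = 8.06 and a rate of 66%. The direction is firm; the exact rate is not.

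**The case against.** The strongest reply is that nothing has been lost. With Time as a three-level factor, dropping Group only reparameterises the model. Fitted means and standard errors are the same, and valid contrasts of change between arms can still be computed. The plan also handles relapse through separate time contrasts, and the later arm comparison can be read as comparing those contrasts between arms, which would be correct. All of this stands. A reader might infer that the model is misspecified or cannot answer the relapse question, or that the plan designates the overall Time*Group test as the relapse comparison. The text supports neither. What remains is that the arm comparison has no named test, and the only listed Group term is described as level differences at each time.

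It is also fair that no offset is given in the documents, that the arms are randomised and receive the same programme, and that the arm comparison is made only after relapse has been found. The last condition does not screen out the problem: equal relapse in both arms is what satisfies it, and a constant offset is no part of it.

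Three further inferences should be resisted:
- That only two product terms would be fitted, forcing the arms to be equal at post-test. This conflicts with a term that allows group differences at the time points, of which post-test is one.
- That Time might enter as the numeric code 1-2-3. The text calls it a factor.
- That the moderator models carry the same fault. The plan says they extend the models above, which include the primary covariance analysis with its Group effect, and nowhere says that lower-order Group terms are dropped.

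**Conclusion.** The point holds in a limited form. The stated reason for leaving Group out is faulty, and the Time*Group term as listed does not correspond to the early-versus-late relapse question. Harm depends on two conditions: the overall test of that term is read as a test of different relapse, and the arms differ by an amount that persists over follow-up. If both hold with a 0.4 SD offset, the false-positive rate is about 41-49% without clustering and about 31-36% with ICC 0.05, against a nominal 5%. These rates rest on the assumed offset, correlation, variance and number of therapy groups. With no offset there is no inflation. The consequence is confined to a conditional, secondary comparison. The primary post-test comparison, the sample size and the overall Time contrasts are not affected, so this is a minor correction.

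**What to change.** State the follow-up fixed effects as baseline, Time, Group and Time*Group, and say that Group is kept for model structure with no treatment claim attached. Name the comparison of relapse between arms: either the 2-df Time*Group test, or the arm differences in change from post-test to 4 months and from post-test to 12 months, with 95% confidence intervals. The cost is one or two sentences of analysis wording. With Time categorical the fitted model stays the same, and no new data or patients are needed.

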Considering the limited number of controlled trials, this study may contribute to filling several knowledge gaps in the sleep therapy literature on comorbid insomnia and persistent pain. First, the present study adds to the literature by focusing on both subjective and objective primary and secondary outcomes. The use of sleep questionnaires, actigraphy- and polysomnography-based sleep measures provides good additional opportunities for examining the role of discrepancies between subjective and objective sleep measures [24]. Secondly, we will provide detailed information about the nature of the intervention, notably its meta-cognitive elements, and the measuring of treatment manual fidelity. Third, the present study aims to be detailed in the search for effects. From the available literature reviews [18, 38, 88], it should be of no surprise to find that the SleepWell intervention will perform better than the TAU control condition because the latter represent an unsystematic and an insufficient degree of health service. The detailed search for effects will focus on the moderator analyses. Such analyses are suitable for exploring sample differences in how the Sleep-Well intervention performs, i.e. whether specific subgroups of eligible patients benefit more from the treatment than others. Additionally, qualitative interviews will be performed among participants who respond favourable to the intervention, and among those who do not or even drop out during the intervention. Such interviews may provide a better understanding of participants’ experiences taking part in sleep intervention studies about their feasibility, relevance and acceptability. This information can help identify potential inconsistencies that might need adjustments to the intervention, particularly in cases where the intervention is successful. Still, participants meet practical challenges that could be addressed through manual or procedural modifications. Such interviews may also contribute to detecting whether patients’ experiences of particular treatment elements elicit changes in how the intervention is conducted. Finally, and for the same purpose, we will also use mediation analyses to identify the most salient possible treatment mechanism underpinning a significant treatment effect. Here, we expect that the meta-cognitive elements may perform equally or better than the cognitive elements; furthermore, these effects will be compared to the behavioural variables included in the study.

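### The three-way term named as the test of who benefits most does not measure treatment benefit; Moderator × Group at week 16 does, but is not named for that role

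*Protocol article*

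**What the plan says.** Everything below is in the protocol article, section {20a}, unless stated otherwise.

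- **Week-16 model.** The primary hypothesis compares the SleepWell arm's post-test with the waiting-list arm's second baseline. It uses an analysis of covariance with the baseline value as covariate, and the therapy group is added as a random factor. Group is in this model; Time is not.
- **Follow-up model.** Time appears only here, with levels "1-post, 2-follow-up at 4 months and 3-follow-up at 12 months". Baseline is again a covariate and not a level of Time. The section says of this model: "Because all patients have received treatment at follow-up, direct testing of general treatment–control effects at follow-up is irrelevant". When it comes to relapse, it describes the comparison as "differences between the SleepWell (early treatment) and the TAU (late treatment) study arms".
- **Moderators.** The exploratory moderator analysis extends the models above it by "adding the moderator variable with its two-way interactions with Time and Group to get a full three-way interaction". The resulting three-way interaction is given a purpose: "that may discern exactly the subgroups defined by the moderator that benefit the most from treatment". Alpha is 0.01.
- **Aim and weight.** Study objectives {7} lists moderators among the exploratory aims, to find subgroups that may or may not benefit. The Discussion says: "The detailed search for effects will focus on the moderator analyses".

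**The concern.** The sentence assigns a question to a term that cannot answer it. Who benefits from SleepWell is a question about treated versus untreated patients, and the only such randomised comparison in the plan is at week 16. The three-way term exists only in a model in which nobody is untreated.

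An analyst who follows the sentence literally could therefore report a null three-way term as absence of moderators, or report a significant one as a responder subgroup when it reflects a different course in early- and late-treated patients. The article treats superiority over TAU as the expected result and places its detailed search on moderators, so this sentence carries more weight than most exploratory ones.

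**Working it through.** **1. Which model can hold the term**

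| | Week-16 model | Follow-up model |
|---|---|---|
| Time levels | none | post, 4 months, 12 months |
| Group contrast | SleepWell vs TAU only | early vs late treatment |
| Untreated patients | TAU arm | none |
| Moderator × Group | difference in treatment benefit | early/late difference by moderator |
| Moderator × Time × Group | cannot be formed | early/late difference in course, by moderator |

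Participant timeline {13} settles what post means for the TAU arm. Week 16 is that arm's second baseline, and its post-intervention assessment is at week 32, after its own SleepWell course. Section {20a} agrees: after crossing over, waiting-list patients follow the same post-test and follow-up plan as the SleepWell arm.

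**2. What each term estimates**

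Let e(m) be the benefit over no SleepWell at moderator level m (0 or 1).

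- Week 16: the TAU minus SleepWell mean is e(m), so Moderator × Group = e(1) − e(0). This is the quantity sought.
- Follow-up: if both arms carry e(m) at all three times, e(m) cancels from every between-arm difference. Moderator × Time × Group = 0 for any e(1) − e(0).

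**3. Numerical check**

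Assumed values: e(0) = 0.3 SD and e(1) = 0.9 SD (true moderation 0.6), benefit held equally in both arms, pre/post correlation 0.5, 40,000 simulated patients, no therapy-group clustering, and ordinary least squares with patient-clustered errors in place of the mixed model.

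- Week-16 Moderator × Group: 0.60 (SE 0.02).
- Follow-up Moderator × Time × Group, two terms: 0.03 and 0.03 (SE 0.02).
- Follow-up Moderator × Group: −0.02 (SE 0.02).
- Follow-up Moderator coefficient: −0.59. With a purely prognostic variable and no effect modification it was −0.62, so it cannot stand in for moderation.

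**4. Precision of the week-16 test**

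The plan's own sample size reproduces first. Inputs from Sample size {14}: d = 0.60, r = 0.5 (R² = 0.25), two-sided alpha 0.05, power 0.80. With residual SD √0.75 = 0.866 and a noncentral t, 34 per arm gives power 0.803, so N = 68. Then 68 × 1.25 = 85, and 85 / 0.8 = 106.25, stated as 106. The sample size is not in dispute.

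For the interaction, assume 85 analysed and an even-split binary moderator:

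SE = √0.75 × √(16 × 1.25 / 85) = 0.866 × 0.485 = 0.42

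Power at two-sided alpha 0.01 (noncentral t, 80 df):

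| True interaction (SD) | Design effect 1.25 | No clustering (SE 0.376) |
|---|---|---|
| 0.4 | 5% | 6% |
| 0.6 | 12% | 16% |
| 0.8 | 24% | 31% |

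By the normal approximation, the interaction detectable with 80% power is (2.576 + 0.842) × 0.42 = 1.44 SD.

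**The case against.** **The right test may already be in the plan.** The sentence extends the models above it, in the plural, and lists a Moderator × Group term. The ANCOVA is one of those models. Extended as written, it would leave Moderator × Group at week 16, which is the test proposed here. This stands, and it rules out the stronger reading a reader might infer, that the plan contains no valid moderator test and that real moderators would necessarily be missed. What remains is that the text gives the role of identifying who benefits to the three-way term, which the ANCOVA cannot contain, and gives no such role to the week-16 term.

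**The zero is built in.** A near-zero three-way term, with power no better than alpha, follows from assuming equal maintenance in both arms. That is correct; the documents do not establish it. If early- and late-treated patients relapse differently by moderator level, the term is not zero. It would then be measuring relapse, so its meaning is wrong for the stated purpose either way.

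**The gain in power is small.** True: even the right test would miss most moderators of plausible size. The case for changing the sentence is that the term should estimate the intended quantity, not that it will detect it.

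**It is exploratory, and detail may sit in an analysis plan.** The exploratory label and the stricter alpha limit the stakes. But the article itself states the term and its interpretation, so this is not a matter of omitted detail.

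**Conclusion.** Wrong as written, and worth correcting. The conclusion that the three-way term does not measure treatment benefit rests only on the article's own model definitions and timeline. That the term is about zero under true moderation rests on the further assumption of equal maintenance in both arms. The power figures rest on an assumed even-split moderator, 85 analysed patients and the plan's design effect of 1.25; at 5%, 12% and 24% for 0.4, 0.6 and 0.8 SD they do not support a claim to identify subgroups exactly.

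A reader might also infer that a significant three-way result will be misreported. That is a risk the wording creates, not something the documents show will happen. The primary hypothesis, its ANCOVA and the sample size are unaffected.

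**What to change.** Replace the moderator sentence in {20a} with, for example:

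*Moderation of treatment benefit is assessed as the Moderator × Group interaction in the week-16 baseline-adjusted model (with the therapy-group random factor), reported as a difference in treatment effect with confidence interval and labelled exploratory. Moderator × Time and Moderator × Time × Group in the follow-up model describe maintenance only.*

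Drop the claim of exact identification of subgroups. The cost is one sentence; no new data, visits or patients are needed.

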### Methods for additional analyses {20b}

Additional analyses serve the purpose of exploring the most effective intervention elements. This will be carried out by using the variables collected for mediation analysis to estimate possible mediation effects. Moreover, to explore the feasibility, relevance and acceptability of the intervention and its separate parts (Table 1), additional analyses include qualitative, semi-structured interviews. We seek to identify the major conceptual dimensions that meaningfully account for all the interview texts, by analysing transcribed interview data using the reflexive thematic analysis approach [84, 85]. The analytic process is dynamic, moving between six analytic phases: (1) reading of the interviews to obtain an overview; (2) marking of text relevant to the research question; (3) sorting text into broader thematic groups; (4) reviewing of thematic text groups for coherence, consistency and meaning related to the research question; (5) definition and naming of themes that capture the meaning of the data; and (6) a final synthesisation. The COREQ criteria for reporting qualitative research will be applied [86]. Patients are eligible for such interviews, whose primary sleep outcome measure shows negligible, and favourable treatment effects, respectively. In each of these subgroups, the number of patients needed to reach data saturation will align with guidelines from a recent systematic review [87].

### Methods in analysis to handle protocol non-adherence and any statistical methods to handle missing data {20c}

The GenLinMixed analysis is favourable for data missing at random as it estimates the parameters based on all available patient data. This reduces biases related to the expected dropout, given that a pattern of missing at random can be presumed. If covariates in the study are correlated with missingness, adjustment for missing is possible by including these as regression covariates.

## Methods: monitoring

### Composition of the data monitoring committee, its role and reporting structure {21a}

A data monitoring committee is not considered relevant for the present study.

### Interim analyses {21b}

No interim analyses are planned for this study. The SleepWell intervention is not expected to cause harm, eliminating the need to arrange stopping procedures to terminate the trial.

### Adverse event reporting and harms {22}

There is no evidence that the intervention may cause harm or serious adverse effects. However, the weekly group sessions with the patients enable continuous monitoring of the study participants and to uncover any negative events from participating in the SleepWell intervention.

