### Intervention descriptions {11a}

The group therapy format for the SleepWell intervention will consist of 6–8 patients in each group, led by two therapists, over seven sessions (~ 1.5 h per session). The first six sessions will be conducted weekly. Eight weeks thereafter, the seventh one is delivered as a consolidation session. The intervention follows a Norwegian group-based CBT-i manual for insomnia [62, 63], which is adapted for use on somatic patients. Between-session homework assignments are described in a corresponding paper workbook that is handed out during the first session. The treatment manual incorporates evidence-based therapeutic components commonly used in sleep intervention protocols [46, 47, 51]. The core components include behavioural procedures, i.e. stimulus control and sleep restriction—and cognitive and metacognitive strategies. Patients will also use implementation intentions [64] to change sleep-related habits.Part 1 introduces the treatment rationale and methods to achieve the intervention’s overall goals. Patients will be introduced to the self-report tools necessary for the daily self-monitoring assignments, which are expected to be completed between sessions. This module also includes psychoeducation on sleep physiology, causes of sleep problems, circadian rhythms and the rationale and practical usage of sleep diaries for recording sleep timing, continuity and duration.Part 2 focuses on establishing good sleep hygiene habits, introducing stimulus control and the practice of sleep restriction and the use of implementation intentions is introduced as a method for changing sleep-related habits.Part 3 addresses cognitive and meta-cognitive factors that maintain sleep disorders, and questions patients’ rationale for their attitudes and beliefs about the need for being occupied with sleep-related worry and rumination.Part 4 emphasises relapse prevention by integrating more functional sleeping habits into daily routines.

Table 1 summarises the main aims and contents/exercises across the four modules and seven sessions of the SleepWell intervention.

**Table 1 Tab1:** Overview of the SleepWell intervention [65, 66]

	**Main objective**	**Content and exercises**
**Part 1**	**Understanding sleep problems and assessment of sleep patterns**	

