### Ancillary and post-trial care {30}

Norwegian patients are covered by the “Norwegian Patient Injury Compensation” arrangement. Since the risk of serious adverse events following participation in the SleepWell intervention is improbable, we do not plan for post-trial care. Measures to compensate for any harms associated with trial participation thus appear irrelevant; hence, there are no plans to establish stopping procedures to terminate the trial or to provide ancillary or post-treatment care. Patients who drop out or do not respond to the SleepWell intervention will be encouraged to contact their GP for further assessment and possible sleep treatment.

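### Harm detection rests on the SleepWell group sessions alone, so harms are not ascertained alike in the two arms before crossover and the trial can give no comparative safety estimate.

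*Protocol article*

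**What the plan says.** Item 22 (adverse events and harms) opens with a prior belief: "There is no evidence that the intervention may cause harm or serious adverse effects". It then gives the detection route: "the weekly group sessions with the patients enable continuous monitoring of the study participants", and these sessions serve "to uncover any negative events from participating in the SleepWell intervention". No other route is named there.

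Three other sections build on the same belief. Item 21b states: "The SleepWell intervention is not expected to cause harm, eliminating the need to arrange stopping procedures to terminate the trial". Item 30 states: "Since the risk of serious adverse events following participation in the SleepWell intervention is improbable, we do not plan for post-trial care", and repeats that no stopping procedures are planned. Item 21a adds: "A data monitoring committee is not considered relevant for the present study". Item 11b nevertheless makes an unforeseen adverse event that seriously endangers the participant a possible ground for discontinuing the intervention.

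On the schedule, item 11a says: "The first six sessions will be conducted weekly", with a seventh session eight weeks later. Items 8 and 13 have TAU patients wait about four months before they enter the programme. Until then, the only extra enquiry described for them (item 6b) concerns health services received.

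**The concern.** A negative event can be judged against treatment only if it is looked for in the same way in both arms. Here the search is tied to attending the intervention, so before crossover it exists in one arm only. The patients have chronic pain and insomnia, and worse pain, low mood or daytime sleepiness will occur in some of them whatever the treatment. An event noticed in a session then has no control rate beside it, and whether it came from the intervention is left to judgement.

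The wording of item 22 also suggests that all participants are watched throughout, which the schedule does not provide. This carries some weight because the trial has no monitoring committee and no stopping procedures, and the reason given in items 21b and 30 is that harm is unlikely. A plan that relies on that expectation should collect the simple data that could bear it out or contradict it.

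**Working it through.** Item 22 states no harm figure to reproduce. The check sets the detection route against the schedule, then shows what unequal capture would do.

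**Patients per arm (item 14).** 68 × 1.25 = 85; 85 / (1 − 0.20) = 106.25, stated as 106, that is 53 per arm. The 68 itself reproduces: analysis of covariance with d = 0.60 and a pre-post correlation of 0.5 has power 0.803 at N = 68, taking alpha 0.05 as two-sided.

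**Coverage to week 16**, counting the first session as week 1 (item 13 has the programme start immediately):

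- SleepWell, 53 patients: sessions 1–6 fall in weeks 1–6. Weekly contact covers 6 of 16 weeks, or 37.5%. One more session follows.
- TAU, 53 patients: no sessions, so 0 of 16 weeks.
- After session 7: no sessions are scheduled, although assessments continue to week 64 (SleepWell) and week 80 (TAU).

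**The gap before session 7.** Item 11a puts session 7 eight weeks after session 6, that is week 6 + 8 = 14. Table 1 says about 4–6 weeks, that is weeks 10–12. The abstract places all seven sessions within 10 weeks. These statements do not agree. On any of them, several weeks pass without a session.

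**What else is collected.**

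- Week 16 repeats the baseline measures in both arms (item 13). These include the BIS, HADS, BPI, Chalder Fatigue Scale and the diary record of daytime fatigue or sleepiness (item 18a).
- Therapists may contact absentees who have consented to this (item 11c), as an adherence measure.
- Patients who drop out during the intervention are invited to interview (items 18a and 18b), about feasibility and acceptability.

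None of these is set up as harm reporting. The last two concern patients in the intervention.

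**Illustration of unequal capture.** The documents give no event risk or capture rate, so all inputs except 53 are assumptions. Let the true risk p be the same in both arms, and let c be the share of events recorded. Expected recorded events are 53 × p × c, and the apparent risk difference is p × (c in SleepWell − c in TAU).

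| p | SleepWell events, c = 0.8 | Apparent difference, TAU c = 0 | TAU c = 0.3 | TAU c = 0.8 |
|---|---|---|---|---|
| 5% | 53 × 0.05 × 0.8 = 2.1 | 4 points | 2.5 points | 0 |
| 10% | 53 × 0.10 × 0.8 = 4.2 | 8 points | 5 points | 0 |
| 20% | 53 × 0.20 × 0.8 = 8.5 | 16 points | 10 points | 0 |

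With no true difference, one-arm capture produces an apparent excess in SleepWell. It disappears only when capture is equal.

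**The case against.** The best defence is that item 22 seeks only events arising from SleepWell, and TAU patients are not exposed to it before crossover. Once exposed, they attend the same sessions. Harm is not listed as an outcome in item 12, and the statistical sections plan no between-arm comparison of it, so no planned analysis is biased. This stands as a limit on the point: what is lost is information, not the validity of a stated test. It does not remove the point, because deciding whether an event came from the intervention needs a background rate, and the waiting arm could supply one.

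It is also fair to say that other contact exists: calls to absentees, dropout interviews, usual clinic or GP care, and a week-16 battery in both arms that could show worsening. This stands too. A reader might infer that TAU patients have no contact at all, or that those who stop attending are lost from view; the documents do not support either. But the protocol does not use any of this contact to ascertain harm.

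Finally, a journal article leaves event definitions and forms to the full protocol. Their absence is not criticised here. The criticism is of what item 22 does state: a single route, described as continuous and as covering the participants generally.

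**Conclusion.** The point holds as a design weakness with a cheap remedy. In the randomised period the stated harm route covers none of the 53 TAU patients, and in SleepWell it is weekly for about 6 of 16 weeks. Harms are not ascertained alike, and the plan as written supports no comparative safety estimate. This rests on reading item 22 as naming the sessions as the sole route and on the session schedule in item 11a. The apparent differences in the illustration rest on assumed risks and capture rates. The primary efficacy comparison is not affected.

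Three stronger readings are tempting and should not be adopted:

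- A reader might infer that the protocol declares SleepWell harmless, or promises to show it. It does not. It says that there is no evidence of harm, that harm is not expected, and that serious events are improbable. These are prior beliefs.
- A reader might infer that the design would make SleepWell look falsely safe against TAU. With capture in one arm only, a raw comparison would tend to make SleepWell look worse. The sound conclusion is that comparative safety cannot be assessed.
- A reader might compute an upper confidence limit for zero events in 53 patients. That limit depends on sample size alone and would be the same after the fix, so it does not measure this problem.

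**What to change.** 1. Add the same short, fixed set of adverse-event questions to the existing online survey, asked identically in both arms at week 16 and at the follow-ups. Tabulate the week-16 answers by randomised arm.
2. From data already collected, report by arm at week 16 the proportion of patients who worsened on the BIS, HADS, BPI, and the fatigue scale or diary sleepiness record, with the definition of worsening fixed in advance.
3. Reword item 22 so that observation in sessions is an addition to this enquiry, and describe its true coverage: SleepWell sessions only, weekly for six weeks and once later.
4. Reconcile the timing of session 7 between item 11a, Table 1 and the abstract.

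The cost is a few survey items, one or two tables and some rewording. The survey becomes slightly longer, and prompted questions will record more minor events, but in both arms alike. Recruitment, sample size and the efficacy analysis stay as they are.
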